***Secondary outcomes***		
Outcome 2	Preventable admission	Preventable admission after being identified at risk by the algorithm
Outcome 3	Readmission (30-days)	Readmission to a Danish hospital within 30 days from a hospital discharge
Outcome 4	Outpatient contacts	Proportion of contacts to outpatient clinics after being identified at risk by the algorithm
Outcome 5	Primary care physicians contacted	Contacts to a primary care physician after being identified at risk by the algorithm
Outcome 6	Death (90-days)	Proportion of diseased citizens identified at risk by the algorithm within 90 days
***Health care utilization and economic outcomes***		
Outcome 7	Changes in utilization and costs of municipal home, nursing and social care services	Information on municipal home, nursing and social care services will be collected as part of the data used in the PATINA algorithm. Costs will be summed from the first date a citizen is identified at risk by the algorithm
Outcome 8	Changes in utilization and costs of planned and unplanned hospital treatment	Information on hospital treatment (planned and unplanned) will be collected from the Danish National Patient Registry. Costs will be summed from the first date a citizen is identified at risk by the algorithm
Outcome 9	Changes in utilization and costs of contacts to primary care physicians	Information on contacts to primary care physicians will be collected from the Danish National Health Insurance Service Register. Costs will be summed from the first date a citizen is identified at risk by the algorithm
Outcome 10	Cost of implementation of the PATINA algorithm and decision support tool	The cost of implementing the algorithm and decision support tool will be calculated as time total time spent for introduction and working with the algorithm for each nurse

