#### PATINA algorithm

The algorithm monitors and analyzes community-dwelling older citizens’ use of municipal home and nursing care with almost real time data (one-week delay). It uses individual administrative data on assigned amount of time (minutes per week) for home care, practical (domestic) help, training/rehabilitation, and nursing care delivered to each citizen.

In each of the three municipalities, a weekly data set with information on health care use during the past week is fed into three separate secure databases via a front-end upload module. Data is then analyzed by the algorithm by comparing home care utilization the last month to a prior period of six months. The algorithm then produces a list of citizens that have triggered the threshold configured for the algorithm. A graph visualizing each citizens utilization of personal care, practical help, training/rehabilitation and nursing care during the last six months is also produced, see Fig. 2.

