#### Analysis of primary and secondary outcomes

Outcomes are shown in Table 2. The primary outcome, proportion of acute admission, will be analyzed using co-variance, repeated measure analysis and logistic regression. A key event is the switch from the usual care to intervention phase. We will treat the intervention regression coefficient as a slopes term to account for potential differences in intervention effects across area home care teams. The analyses will be adjusted for relevant confounders such as age, gender, co-morbidity, functional level and frailty.

For secondary outcomes (Table 2) 2, 3, 4, 5 and 6 we will use logistic regression to analyze occurrence of event. Citizens, who relocate to another municipality, move into a care home, or die during the study period will be excluded from the analyses. Models for acute admission will be used and the incidence of acute admission will be analyzed using logistic regression. The analysis will be adjusted for confounding factors such as age, gender and co-morbidity. We will stratify the analyses by municipalities and area home care teams to control for differences between these.

When analyzing readmission between the intervention and control group we will focus on both the 30-day readmission rate (outcome 3) and 90-day readmission rate (outcome 4). The index-admission will be defined as any admission to a Danish hospital during the study period. Citizens with multiple hospital admissions can have several index admissions but only one readmission per index admission.

Changes in citizens health service utilization (outcome 7, 8 and 9) will be evaluated in order to assess changes in costs of care and treatment in the primary and secondary health care sector. We will analyze the average cost per citizen, as well as analyses of the change in costs in primary and secondary health care. We will also analyze the costs of implementing the PATINA algorithm and decision support tool (outcome 10). This will be done by summing up the time spent on project related activities by both nurses and project coordinators in each municipality. The costs of implementing the algorithm will be reported as the total cost of the intervention with a 95% confidence interval.

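### Outcomes 7-9 are titled as changes in cost but measured only as a sum from the first flag onward, so the change is undefined and pre-flag care level is not used in the stated measure

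*Protocol article*

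**What the plan says.** In the protocol article, Table 2 (Health care utilization and economic outcomes) names the three outcomes as follows:

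- Outcome 7: "Changes in utilization and costs of municipal home, nursing and social care services"
- Outcome 8: "Changes in utilization and costs of planned and unplanned hospital treatment"
- Outcome 9: "Changes in utilization and costs of contacts to primary care physicians"

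The outcome-measure column gives a data source for each and then repeats one rule for all three: "Costs will be summed from the first date a citizen is identified at risk by the algorithm". It mentions no value from before the flag.

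The section on analysis of primary and secondary outcomes states the purpose: "Changes in citizens health service utilization (outcome 7, 8 and 9) will be evaluated in order to assess changes in costs of care and treatment". It then lists two quantities: "We will analyze the average cost per citizen, as well as analyses of the change in costs in primary and secondary health care". It does not say from which period, or against which comparator, the change is taken.

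Two other sections bear on what is available. The section on the PATINA algorithm says that the flag comes from "comparing home care utilization the last month to a prior period of six months", and Table 2 takes outcome 7 from those same data. The Data collection section says that the trial data will be linked to national registers, which supply outcomes 8 and 9.

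**The concern.** The title promises a change and the measure supplies a level. A citizen with heavy, long-standing home care and one with light care both enter the average cost at their raw post-flag level, and nothing in the stated measure separates prior level from what followed the flag.

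Two things are at stake. The first is meaning. With the change undefined, several different quantities would fit the text, and for outcome 7 the choice matters because the flag itself is fired by a rise in home care use. The second is precision. Costs vary widely between citizens for reasons that predate the flag, and the stated measure leaves that variation in the error term. The Discussion hopes to use these costs to point to economic incentives for the tool, so both the definition and the precision deserve a few lines.

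**Working it through.** **No figure to reproduce.** The article gives no mean, standard deviation, pre/post correlation, effect size or power for outcomes 7-9. Its only power statement concerns acute admission. The check is therefore a comparison of passages, followed by an illustration with an assumed input.

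**Step 1: can the stated measure give a change?** By the Table 2 rule, each citizen contributes one sum, which starts at the first flag. Take three citizens with the same post-flag sum of 300 (arbitrary units) and pre-flag costs of 200, 300 and 400. Their within-citizen changes are 300 - 200 = +100, 300 - 300 = 0 and 300 - 400 = -100. The stated measure records 300 for all three. A within-citizen change cannot be recovered from it.

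**Step 2: can it give another kind of change?** Yes. Crossover from usual care to intervention is at a randomised time (Study design section). Post-flag cost can therefore be compared between intervention and usual-care periods without any baseline, provided that flags are also generated in usual-care periods and that time and clustering are handled. The Discussion commits to adjusting for both. This contrast may be what the authors mean, but the analysis text lists the change in costs alongside the average cost per citizen, as if it were a second quantity, and does not say how the two differ.

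**Step 3: are pre-flag values available?** For outcome 7, yes: the algorithm works on a six-month reference period before the last month. For outcomes 8 and 9 the article shows linkage to registers but states no look-back for costs, so availability is likely but not shown.

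**Step 4: what would using them gain?** Let *r* be the correlation between a citizen's pre- and post-flag cost. It is not in the document and is assumed here. With equal variance before and after and no clustering, the variance relative to a post-flag-only analysis is:

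- change score: 2(1 - *r*)
- baseline as covariate: 1 - *r*², so the standard-error ratio is √(1 - *r*²)

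| Assumed *r* | Post-flag only | Change score | Baseline as covariate | SE ratio, covariate |
|---|---|---|---|---|
| 0.4 | 1.00 | 2(0.6) = 1.20 | 1 - 0.16 = 0.84 | √0.84 = 0.917 |
| 0.5 | 1.00 | 2(0.5) = 1.00 | 1 - 0.25 = 0.75 | √0.75 = 0.866 |
| 0.7 | 1.00 | 2(0.3) = 0.60 | 1 - 0.49 = 0.51 | √0.51 = 0.714 |

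For *r* from 0.4 to 0.7, the covariate approach removes 16% to 49% of citizen-level variance and lowers the citizen-level standard error by 8% to 29%. A raw change score helps only if *r* exceeds 0.5, and at 0.4 it does worse than no baseline at all.

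**Step 5: which baseline window?** The flag selects citizens whose last month rose above the preceding six. That month is high partly by selection, so an uncontrolled change measured from it would be affected by regression to the mean. The six months before it are the algorithm's own reference. They also end before the first flag, and so before any assessment that the flag prompts for that citizen; adjusting for them does not adjust away the effect.

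**The case against.** The strongest reply is that nothing is broken. In a trial with randomised crossover times, change can naturally mean the difference between usual care and intervention, and that contrast needs no baseline. The analysis section does commit to a change analysis, and the summing rule is worded for costs, not utilisation. Chance imbalance in prior care level is covered by a correctly computed standard error. Covariates for economic outcomes are commonly left to an analysis plan or full protocol, neither of which is shown.

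Most of this stands. A reader might infer that the trial measures no change at all, that it throws away its pre-flag data, or that prior care level will be mistaken for an effect on cost. The documents support none of these. A change analysis is promised, the text is silent on the use of pre-flag data, and randomised timing protects the between-phase contrast. Nor does any passage propose the trigger month as baseline; the regression-to-the-mean point is a reason to fix the window, not a fault already in the plan.

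What the reply does not remove is the mismatch in what is stated. Three outcomes carry a title that their only cost measure does not deliver, and the analysis text repeats the word without defining it. That is a matter of wording already fixed in the article, not of detail left for later.

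**Conclusion.** The point holds as a mismatch between title and measure, together with a missed gain in precision. Table 2 and the analysis section need to be reconciled, because the stated post-flag sum gives no within-citizen change and the change in costs has no defined reference. The between-phase comparison of post-flag cost is valid, on the assumption that flags are recorded in usual-care periods too, but it is less precise than it could be.

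The 8-29% reduction in standard error is illustrative. It rests on an assumed correlation of 0.4 to 0.7, which need not be the same for municipal, hospital and physician costs, and it applies to citizen-level variation only. With 20 home care teams crossing over in steps, cluster and period variation also enter the treatment-effect standard error, so the gain there may be smaller. The outcomes concerned are not primary. This is a worthwhile, inexpensive improvement and does not threaten the trial's main result.

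**What to change.** Reword Table 2 and the analysis section so that they agree:

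- Define the effect for outcomes 7-9 as the intervention versus usual-care difference in post-flag cost, adjusted for the same citizen's cost in the six-month reference period before the trigger month. State that this is what change means.
- Exclude the trigger month from the baseline, since the flag selects on a rise in that month.
- Use the algorithm data for the outcome 7 baseline and the linked registers for outcomes 8 and 9, after confirming that the linkage reaches back far enough.
- For citizens with under six months of data, use a shorter look-back or an indicator, and fix which in advance.

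The cost is a few lines of text, a six-month look-back in data that are held for outcome 7 and should be obtainable by linkage for outcomes 8 and 9, and a rule for citizens with a short history. If the baseline is not wanted, the minimum is to rename the three outcomes as post-flag utilisation and costs and to state the between-phase comparison.

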***Process outcomes***		
Outcome 11	Barriers and facilitators for nurse’s acceptance and use of the algorithm	Data will be collected as a three-wave survey, which will be integrated in SW-CRT design and follow the step-wise implementation of the algorithm in each of the tree municipalities

#### Recruitment and enrollment

The management in each of the three municipalities have approved their participation in the study. To support the project manager, a project coordinator has been appointed in each municipality. All community nurses and their immediate superior have participated in an information meeting, with the purpose of explaining the background of the study, enrollment and training procedures. Information about the PATINA algorithm and decision support tool is kept to a minimum.

When an area home care team is randomized to receive the intervention the project manager (AF) and project coordinator meet with the community nurses that are selected for participation in the intervention. The meeting has a scheduled time frame of 2 h and is held twice, seven days apart. The purpose of the first meeting is to introduce the nurses to the background of the study, their role and introduction to the PATINA algorithm and decision support tool. In the second meeting, nurses will complete a practical training session using the PATINA algorithm and decision support tool.

Prior to the initiation of the study the three municipalities have signed a collaborative agreement, which in details describes each municipality’s role and contribution to the study, as well as duty of confidentiality, intellectual properties and publication rights. The trial will only be discontinued if the three municipalities, the Region of Southern Denmark or an ethical committee finds it necessary for regulatory or medical reasons.

#### Data collection

Data will be collected continuously on a weekly basis during the course of the study. In a typical week nurses in an intervention area home care team each receive a list of citizens at risk on a Monday morning. The nurses have two days (until Wednesday) to assess each citizen’s health situation using the ‘PATINA decision support tool’. On the fourth day (Thursday), the project manager (AF) carries out a weekly quality assessment of the gathered data. If data is missing or major errors are identified the project coordinator contacts the nurse responsible for the entered data to discuss the case, and if needed, adjust accordingly.

In accordance with Danish laws on data protection study data will be collected and stored in REDCap (version: REDCap 9.1.15 -© 2020 Vanderbilt University) [31, 32], an electronic data capture tool hosted at OPEN at Odense University Hospital, the Region of Southern Denmark. Data from the PATINA algorithm and decision support tool will be linked to data from Danish national health registries using the citizens unique social security number. The registers include data from the National Patient Registry (history of disease, diagnosis, acute or elective admissions, readmissions, outpatient care and hospital treatment), the National Health Insurance Service Register (services from primary care physicians, the Register of Medicinal Product Statistics, and the Danish Civil Registration System (age, gender, marital status and more).

### Data analyses

#### Sample size and statistical power

The three municipalities, Odense, Svendborg and Kerteminde, provide access to data on all citizens age 65+ and over, who receive home or nursing care, yielding an expected study population between 5.500–6.000 individuals.

We have calculated the power of the study using an assumption of a one-sided significance level of 0.05 and equal sample size between the intervention and control group. It has not been possible to identify previous studies investigating the effects of monitoring utilization of home care combined with an intervention to prevent acute admission. Thus, we use a conservative estimate of 10% difference in number of acute admissions between the intervention (10.8%) and control group (12%) [38]. On the basis of these assumptions the power in each of the three municipalities seems rather modest (Odense β = 0.15, Svendborg β = 0.12, Kerteminde β = 0.1). Across the three municipalities the power is somewhat greater, the β will at least be 0.22 depending on the timing.

The power calculation was carried out using STATA 16 and the command” .steppedwedge”, as described by Hemming and Taljaard [39].

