### Study procedures

#### Randomization and implementation

The stepped-wedge design allows all 20 area home care teams across the three municipalities to receive the intervention, but at different time points according to randomization. Following the time schedule, a new area home care team is included in Kerteminde Municipality approximately every 12 weeks, in Svendborg Municipality every six weeks, and in Odense Municipality every four weeks (Fig. 1). The computer-generated stepwise randomization is carried out by a statistician from Open Patient data Explorative Network (OPEN), Odense University Hospital, Region of Southern Denmark.

All three municipalities are made aware of the randomization procedure prior to study start. However, the starting date for the intervention exposure will not be announced until four weeks prior to implementation start.

In this study it is not possible to blind neither nurses or other health care professionals, nor the management in each municipality. However, nurses and the management are instructed only to talk about the project with coworkers within their own area home care team, and not with colleagues in other teams.

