#### Statistical analyses

Data management and statistical analyses will be carried out using SAS version 9.4 software (SAS Institute Inc., Cary, NC, USA) and STATA version 16 (StataCorp LLC, Texas, USA). The analyses will be supplemented by modelling and graphics using “R” software (Version 3.6.1) [25].

Data analyses will be conducted according to intention-to-treat principles and include all eligible patients with available outcome data. The analyses will be conducted according to the randomization schedule. Citizens’ characteristics will be reported using numbers/percentages, means (SD), and medians [IQR]. Differences between the intervention and control groups will be calculated using chi2 tests, Student’s t-test, or Kruskal-Wallis test, as appropriate. The statistical significance threshold for all tests will be set to *P* < 0.05.

When presenting the results of our study we will use suiting EQUATOR network guidelines such as the CONSORT 2010 statement [40] with the extension for stepped wedge cluster randomized trials [41].

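### Powers are printed as β and computed at one-sided 0.05, while the analysis threshold has no direction: minimum power is 0.22 one-sided, and about 0.14 if the primary test is two-sided

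*Protocol article*

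**What the plan says.** The section on sample size and statistical power fixes four things. Power is calculated "using an assumption of a one-sided significance level of 0.05" with "equal sample size between the intervention and control group". The event rates are 12% under control and 10.8% under intervention, a 10% relative or 1.2-point absolute difference. The expected population is 5,500 to 6,000. For single municipalities the section concludes that "the power in each of the three municipalities seems rather modest (Odense β = 0.15, Svendborg β = 0.12, Kerteminde β = 0.1". It then says: "Across the three municipalities the power is somewhat greater, the β will at least be 0.22 depending on the timing".

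The section headed statistical analyses states: "The statistical significance threshold for all tests will be set to" P < 0.05. It names chi-square, Student's t and Kruskal-Wallis tests for group differences. The section on primary and secondary outcomes names logistic regression, among other methods, for acute admission and gives no sidedness. Nowhere does the article declare a one-sided analysis.

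**The concern.** There are two separate faults in how the design's sensitivity is reported.

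- **Label.** β normally means the type II error, so an overall β of 0.22 reads as 78% power, close to the usual target of 80%. The surrounding sentences make sense only if the numbers are powers. In that case the design has far less sensitivity than the symbol suggests.
- **Sidedness.** Power is planned at one-sided 5%. The analysis threshold is 5% with no direction attached, which most readers will take as two-sided. If so, the power figures do not describe the test that will be carried out.

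At stake is how a non-significant primary result is read. Someone who believes that power was 78% may take it as evidence of no benefit. At the stated minimum power, such a result would be the likely one even if the planned effect were real.

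**Working it through.** **Inputs.** From the sample size section: one-sided α = 0.05; rates 12% and 10.8%; printed values 0.15, 0.12, 0.10 and at least 0.22. From the statistical analyses section: P < 0.05, no direction. The intracluster correlation (ICC) and cluster-period size are not given, so the printed figures cannot be reproduced from the stated inputs alone. Steps 1 and 3 do not need them.

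**1. Are the values powers or type II errors?**

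For one-sided power π, the standardised effect is z = Φ⁻¹(π) + 1.645. Treating the municipalities as independent information on one common effect, the squares of z add.

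*Read as powers:*
- Odense 0.15 gives 0.608; Svendborg 0.12 gives 0.470; Kerteminde 0.10 gives 0.363.
- √(0.608² + 0.470² + 0.363²) = 0.850.
- Overall power = Φ(0.850 − 1.645) = 0.213, or 0.20 to 0.23 allowing for rounding of the inputs. The article prints at least 0.22.

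*Read as type II errors:*
- Powers would be 0.85, 0.88 and 0.90. Kerteminde, with 3 of the 20 teams, would be the best powered and Odense, with 10, the worst.
- The pooled trial, at 0.78, would have less power than any of its parts, although the article says that it has more.
- Combined as above, the pooled type II error would be about 0.001, not 0.22.
- Even without clustering, 78% one-sided power for 12% against 10.8% needs about 8,195 per arm. About 2,750 to 3,000 per arm are available.

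Only the first reading is coherent.

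**2. Cross-check with a stepped-wedge model.**

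Assumptions: 20 teams, 10 steps of two, 11 periods, fixed period effects, the population of 5,500 to 6,000 split over the periods, ICC 0.01 to 0.10. One-sided power is 0.20 to 0.23. With a population of 5,750 divided in proportion to residents over 65 and ICC 0.05, the municipal powers are 0.164 (Odense), 0.111 (Svendborg) and 0.082 (Kerteminde), each within two points of the printed value.

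Counting the whole cohort afresh in every period instead gives 0.84 to 0.98 overall (ICC 0 to 0.10) and 0.70 to 0.76 for Odense (ICC 0.001 to 0.05). That matches neither the printed powers nor the description of them as modest.

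**3. Conversion to two-sided 5%.**

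Two-sided power = Φ(z − 1.960) + Φ(−z − 1.960).

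| | One-sided (printed) | z | Two-sided |
|---|---|---|---|
| Overall | at least 0.22 | 0.873 | at least 0.141 |
| Odense | 0.15 | 0.608 | 0.093 |
| Svendborg | 0.12 | 0.470 | 0.076 |
| Kerteminde | 0.10 | 0.363 | 0.065 |

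Without the opposite tail, the overall figure is 0.139.

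**4. What the minimum implies, in percentage points.**

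- Standard error = 1.2 / 0.873 = 1.375.
- 95% CI half-width = 1.960 × 1.375 = 2.7.
- Difference detectable with 80% two-sided power, standard error held fixed: (1.960 + 0.842) × 1.375 = 3.85, that is 12% to about 8.1%, a 32% relative reduction.
- If the binomial variance is allowed to fall with the intervention rate, the answer is about 3.7, roughly a 30% relative reduction.

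Because 0.22 is printed as a minimum, the standard error, half-width and detectable difference here are upper limits.

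**The case against.** The strongest reply is that the article is open about low power. It introduces the figures as power, calls them modest, and says that power improves as the number rises. A careful reader would see that the symbol is wrong, and no figure has been shown to be miscalculated. That stands: the fault is a label and an unreconciled sidedness, not a computing error. But β is a defined quantity, and the value printed beside it is close to the complement of the true one. Readers who lift the number will lift the wrong one.

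The second reply concerns sidedness. The analysis section never says two-sided. The non-directional tests are named directly after the reporting of citizens' characteristics, and the primary model is described in another section without a direction. An analysis plan that is not shown may settle the matter. This also stands. A reader might infer that the primary test is two-sided as a matter of record; the documents do not support that. They support only this: the planning α is one-sided, the threshold for all tests carries no direction, and the two have not been reconciled. The figure of 0.14 is therefore conditional.

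**Conclusion.** The point holds. The four figures are powers (1 − β). The overall type II error is at most about 0.78, not 0.22. If the primary test is two-sided at 5%, the minimum power is about 0.14. This conversion rests on the normal approximation and on 0.22 being one-sided power. It does not depend on the unstated ICC.

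Three stronger readings are tempting and should not be adopted:

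- A reader might infer that power *is* 22%, or 14%. The article says at least 0.22, depending on timing, so both are floors.
- A reader might infer that the type II error is at least 0.78. The bound runs the other way: power of at least 0.22 means a type II error of at most 0.78.
- A reader might infer that a null result is near certain. With the planned effect, the chance of non-significance is at most about 0.86 two-sided (1 − 0.14) or 0.78 one-sided (1 − 0.22). That is likely, not certain.

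**What to change.** 1. Replace β by power (1 − β) for all four figures.
2. State whether the primary test is one- or two-sided, in both the sample size and the statistical analyses sections, so that they agree.
3. Restate power at that level. Suggested text: *Power is at least 0.22 at one-sided 5%, equivalent to at least about 0.14 at two-sided 5%. At that minimum, the difference detectable with 80% power (two-sided) is at most roughly 3.7 to 3.9 percentage points, against the planned 1.2.*
4. Add that interpretation will rest on the estimate with its 95% CI, and that non-significance will not be read as absence of effect.

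The change touches text only, with no effect on design, data or estimation. Its one cost is that the stated sensitivity looks less favourable.
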